## The OptiBreech-ECV Trial

This study will evaluate the feasibility of comparing OptiBreech care with the standard care pathway, offering and encouraging ECV, by randomising women within the cohort who consent in a pilot trial. The results will be compared with each other, and to the outcomes for women within the cohort who were otherwise eligible for but did not consent to randomisation. It is a pragmatic trial designed to compare the care pathways as they would be delivered were the OptiBreech model to be implemented as policy. Women and birthing people who participate will retain their usual rights to decline the care offered.

## Flowchart

Figure 1: Study Design Flowchart

## Research Timeline

Figure 2: Research Timeline

# Participant Selection

## Sites

All NHS sites who are providing OptiBreech Care are eligible to contribute data to the cohort study.

Site requirements for participation in the pilot randomisation include:

1. Recruited a minimum of 5 women to OptiBreech 1 or the non-randomised cohort of OptiBreech mTC
2. Achieved at least 90% fidelity to the intervention (attendance of someone with training and/or proficiency, <5 minutes from pelvis to head and use of maternal movement and effort prior to hands-on assistance) for a minimum of 5 vaginal breech births
3. Able to present a plan for recruitment and randomisation for a minimum of 2 women per month who provide fully informed consent to taking part in the study, immediately following diagnosis of breech presentation by USS, prior to counselling for ECV/mode of birth
4. Able to ensure a member of the OptiBreech team is available to provide counselling for women randomised to ‘offer OptiBreech Care’
5. Able to include the Physiological Breech Birth Algorithm in annual mandatory training activities for all staff. This should cover: The recommended 7-5-3 minute time limit guidance; actions in response to delay in second stage, including delay on the perineum; physiological neonatal transition, including initiation of resuscitation where required with umbilical cord intact; effective communication; and maintaining a helicopter view
6. Identification of a Breech Specialist Midwife and/or Obstetrician with dedicated time to co-ordinate OptiBreech care and training, ability to deliver the physiological breech birth training package and commitment to participate in on-going professional development seminars provided by the research team throughout this trial.

Sites will be able to demonstrate adherence to these criteria during their participation in the OptiBreech 1 study.

We will initially include 2 Trusts, including 3 hospital sites, in the randomisation pilot. Approximately 4% of women have a breech pregnancy at term, and we can expect at least half of these to be eligible for randomisation. Feasibility testing as part of OptiBreech 1 indicated that we can anticipate half of these again, or 1% of all women, will consent to randomisation in this study. Sites will be expected to recruit a minimum of 10 participants willing to be randomised over a 6 month period.

## Participants

### OptiBreech mTC – Cohort inclusion criteria

Eligibility to participate in the cohort study will include:

- Live, singleton pregnancy with a breech-presenting fetus confirmed by ultrasound scan;
- Over 16 years of age;
- Referred for specialist care for breech presentation antenatally from 32 weeks;
- Breech presentation from 37 weeks discovered in labour;
- Requesting or preferring a vaginal birth; and
- Giving informed consent to participate to contribute data to the cohort study. *(Note: For women in active labour, consent should be sought AFTER the birth; see below.)*

### Cohort Exclusion criteria

The following will be excluded from the cohort study:

- Absolute reason for caesarean section already exists (e.g. placenta praevia major);
- Requesting a caesarean section prior to recruitment;
- Multiple pregnancy;
- Life-threatening congenital anomaly; or
- Not consenting to contribute data to the cohort study

### OptiBreech-ECV Trial – Additional inclusion criteria for randomisation

In addition to the cohort inclusion criteria, eligibility for randomisation will include:

- Consent to randomisation.

### Trial exclusion criteria

Exclusion criteria include any contraindication listed in the RCOG guidelines for external cephalic version and/or management of breech presentation at term, including:

- Has already had an ECV attempt prior to recruitment
- Rhesus isoimmunisation
- Current or recent (less than 1 week) vaginal bleeding
- Evidence of antenatal fetal compromise, including abnormal electronic fetal monitoring
- Rupture of the membranes
- Hyperextended neck on ultrasound
- Estimated fetal weight less than 2000 g or less than 10^th^ centile at recruitment (if a growth scan has been performed)
- Estimated fetal weight greater than 3800g or over 95^th^ centile at recruitment (if a growth scan has been performed)
- Standing / footling presentation at the time of recruitment, defined as hips extended and breech above the inlet to the pelvis or not longitudinal;
- Any indication at the time of recruitment for induction to be recommended prior to 41 weeks of pregnancy, e.g. gestational diabetes, obstetric cholestasis, advanced maternal age;
- Breech diagnosed for the first time in labour; and
- 2 or more previous caesarean sections.

# Study procedures

## Participant recruitment

OptiBreech cohort sites should establish their own pathways for screening, approaching and consenting potentially eligible women and birthing people. An ideal pathway would look like this (Figure 1):

1. Breech presentation is suspected on palpation. The woman is referred for an ultrasound scan to confirm. When a clinician makes a referral, the woman should be directed to the information, including the approved Participant Information Sheet, available on the feasibility study’s website (https://optibreech.uk).
2. Women booked for a presentation scan are initially screened by a member of the clinical team providing direct clinical care, and those eligible for recruitment are flagged.
3. Breech presentation is confirmed on ultrasound. Immediately after this scan, the woman is asked if she would like to participate in the study. She is offered an opportunity to ask questions and consent is obtained, by the staff member if authorised to collect consent on the delegation log, or a member of the research team.
4. If the woman is also eligible to be randomised to standard care or OptiBreech care, based on the consents she has given and her scan results, she is randomised. The woman should receive a copy of all relevant Participant Information Sheets and a copy of her fully executed consent form.
5. She begins the care pathway she is randomised to. A copy of the GP letter, relevant Participant Information Sheet(s) and Consent form is sent to the GP.

This is ideal because OptiBreech care is a care pathway intervention, and the care pathway begins when the woman is first counselled.

Eligibility for randomisation among the cohort participants is automatically captured in the eCRF during the recruitment process. We are opting not to use an additional screening log, although individual sites may wish to create their own, as this information is already automatically captured on Edge. Having an additional log has not been shown to increase recruitment but does add significantly to the research team’s workload.^63^ Instead, we will monitor site activity through absolute recruitment and adherence rates. We will use a delegation log, and all local research team members involved in recruitment should be listed on this log once the local PI has ensured they have received training. As this is an intervention study, all those taking consent for participation in the study should have current GCP training in place, or have completed the OptiBreech training that includes GCP-lite training relevant to this study, and be listed on the delegation log.

Consent will be completed directly through the study’s on-line database, provided by MedSciNet. The consent form is available in an electronic format on the study database to which participants have direct access, and they will sign consent online. Access will be provided via the e-mail address given by potential participants for this purpose. The system will confirm who accessed the database and the date. The consent form will be countersigned by separate access by the person taking consent, so that the data and time are recorded. This may be completed face-to-face or asynchronously through the online access provided. A fully executed version is saved within the database. A copy is exported to be stored in the participant's medical record, and the participant can download a copy for their own records using their direct access.

Consent will ideally be a research midwife, but because consent is taken prior to the start of their breech care pathway, it can be taken by any healthcare professional who has completed GCP training or OptiBreech GCP-lite training and signed the delegation log. When women are enrolled, they will be given login information so that they can enter their details directly onto the database. These login details will later be used to complete the follow-up surveys if women have consented to receive these. Consent will be confirmed on-line by the health care professional who has taken consent. Paper copies of the PIS and Consent forms will be provided in case the on-line version fails or is inaccessible.

A copy of the consent form will be sent to the woman and local research team, to be filed in the woman’s notes. Where paper-based consent forms have been used, a scanned copy should be sent by secure electronic transfer or encrypted NHS e-mail to the core research team.

PPI work indicated that enabling women to access participation in this study if they wish was a priority. All PPI group participants had experience of either their own difficulty seeking support for a vaginal breech birth, or experience of supporting women who were having difficulty accessing care for a vaginal breech birth. Additionally, approximately 1/3 of the participants in OptiBreech 1 were self-referrals, who transferred care from another Trust to receive support for a vaginal breech birth within a hospital participating in OptiBreech 1. Therefore, if a Trust feels it is ready to accept self-referrals, contact information for their Breech Clinic will also be made available via the study’s website, for women who may wish to self-refer. Women may self-refer either internally or from a different Trust if they would like to participate in the research. In this case, women would be screened by OptiBreech staff for suitability.

The minimum recruitment target for each site in this 6-month pilot trial is 10 women who consent to randomisation. Each additional recruitment to the cohort study (non-randomisation) will count as an accrual, but the minimum recruitment target is based on women who consent to randomisation.

### Breech presentation diagnosed in Labour

Within sites where routine 3^rd^ trimester scans are not offered, breech presentation is diagnosed for the first time in labour among 20-30% of the population.^64,65^ Almost all of these would be eligible for the OptiBreech Cohort, although not randomisation. Therefore, it is appropriate to include their outcomes within the cohort, if consent is given.

In these cases, the potential participant will be informed about the study approximately 24 hours after the birth during a debrief of the birth itself. They will then be asked for consent to include their data. Where care recipients do not provide consent, their data will not be used. Local PIs should establish a system to identify unplanned VBBs so that they can be included in the cohort study.

This procedure is consistent with the current RCOG guidance on “Obtaining Valid Consent to Participate in Perinatal Research Where Consent is Time Critical.”^66^ It was specifically discussed at a PPI group meeting on 15 July 2020 and modified based on the group’s feedback to ensure the request for consent was also accompanied by a full debrief of the woman’s birth experience. Women in the group who had experienced an undiagnosed breech birth felt this would have been particularly helpful to them, resulting in a consent process that was both beneficial for the women themselves as well as for the research. We have piloted this procedure in OptiBreech 1.

Completion of the debrief is monitored through the CRF.

Where an adverse outcome has occurred during an unplanned vaginal breech birth, it is important to include these outcomes in the study, subject to consent, whether an OptiBreech team member was present or not. However, this requires very sensitive counselling, and the woman may wish to decline follow-up surveys. This should be offered by the Breech Lead Obstetrician or Breech Lead Midwife and further referrals for counselling and support should be made as appropriate.

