## Screening Procedures

The clinical team with a duty of care for the woman should review the potential participant’s medical record prior to the scheduled ultrasound scan appointment to screen for eligibility, and if eligible, ensure they have information about the research prior to attending. They should also ensure research staff are alerted and available to take informed consent. If the woman is eligible for the cohort and consents to randomisation, the eCRF will guide the research team member through the eligibility criteria.

However, one of the challenges to studying breech care is the variety of times at which women are diagnosed and/or referred for care. In some Trusts, women are referred for care from as early as 32 weeks so that they can be counselled about using moxibustion and/or postural interventions to encourage baby to turn head-down. In some pregnancies, the breech presentation is not diagnosed until an ultrasound scan is performed for other reasons at a later gestation. Some breech presentations remain undiagnosed until the woman is in labour. And some women will transfer care to access support for a vaginal breech birth after multiple failed ECV attempts elsewhere. In some instances, the circumstances will mean the women are ineligible for randomisation but can be included in the cohort. In the first two instances, women may still be eligible for randomisation and should be offered it as early as possible in their care. Having had an ECV in this pregnancy, prior to recruitment, is an exclusion criteria for randomisation but not the cohort should women be identified as eligible later than the idea recruitment point.

Because of this variability, all clinical staff who may encounter women at these various stages should be aware of the research and how to refer to the research team. This will include all clinical staff providing ultrasound scans for breech presentation, such as midwives, obstetricians and sonographers. And any staff referring women for scans should provide information about the research in advance.

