**Cohort analysis**

Potential primary outcome = composite perinatal death or serious morbidity (maternal and neonatal) following enrolment

1. Groups 1: ECV (grey) versus planned VBB with no ECV (dark green). Cochrane review: Incidence of Apgar <7 at 5 minutes, 44/1000 following ECV, 70/1000 following no ECV, considered equivalent.
2. Groups 2: VBB with OptiBreech care (planned and unplanned) versus VBB without OptiBreech care (planned and unplanned) (all green, subgroups). In the Term Breech Trial,^45^ this rate was 5%. In the PREMODA cohort study,^71^ it was 1.6%.
3. Additional comparisons: all planned CS (all blue) vs all planned cephalic birth after ECV (yellow) vs VBB with OptiBreech care vs VBB without OptiBreech care (all green)
   1. Planned cephalic birth after ECV as control

Potential secondary outcome = mode of birth

1. Comparison: ECV attempted (grey) versus planned VBB with no ECV (dark green)
2. Comparison: VBB with OptiBreech team versus no OptiBreech team present (all green, subgroups)

We will report on incidence rates for all of these outcomes that may be used as comparators.

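### For breech first found in labour, the only identification system the protocol names is triggered by vaginal breech birth, so this cohort stratum is selected on an outcome it reports

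*Protocol*

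**What the plan says.** Section 7 of the protocol (OptiBreech mTC – Cohort inclusion criteria) lists "Breech presentation from 37 weeks discovered in labour" as a route into the cohort, together with "Requesting or preferring a vaginal birth; and" the remaining consent condition. Neither criterion depends on how the woman delivers.

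Section 8 (Breech presentation diagnosed in Labour) puts the size of this group, at sites without routine third-trimester scans, as follows: "breech presentation is diagnosed for the first time in labour among 20-30% of the population". It then says: "Almost all of these would be eligible for the OptiBreech Cohort, although not randomisation". Consent is sought after delivery: "the potential participant will be informed about the study approximately 24 hours after the birth during a debrief of the birth itself".

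The same section gives one case-finding instruction: "Local PIs should establish a system to identify unplanned VBBs so that they can be included in the cohort study". Its paragraph on adverse outcomes likewise speaks only of unplanned vaginal breech births. No corresponding system is described for a woman diagnosed in labour and then delivered by caesarean.

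Two other places bear on identification. Section 8 (Participant recruitment) chooses not to require a separate screening log. Section 8 (Screening Procedures) places a general duty on staff: "all clinical staff who may encounter women at these various stages should be aware of the research and how to refer to the research team".

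**The concern.** Eligibility is defined by the time of diagnosis and by preference. The named search is defined by the result. A woman who wanted a vaginal birth, was found to have a breech baby in labour and had a caesarean belongs in the cohort, but the stated system would not look for her. A woman with the same history who delivered vaginally would be found.

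Mode of birth is the second secondary outcome in section 5, and the maternal composite in the same list includes injuries at the uterine incision that arise only at caesarean delivery. The Introduction itself notes that emergency caesarean carries higher maternal risk when breech is first discovered in labour. So the women likely to be missed are a group the protocol regards as being at increased risk.

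Section 4 (Patient and public involvement) presents the cohort as a source of prospective intention-to-treat data on rare safety outcomes. Section 6 presents the database as the start of a long-term multi-centre cohort. A rule that finds cases by their outcome does not serve the first purpose for this stratum, and it would be carried forward under the second. Because no log is required, and no count of labour-diagnosed women by mode of birth is specified, the selection could not be measured afterwards.

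**Working it through.** The protocol gives no figure for this point, so there is nothing to reproduce. The check has three parts.

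**1. The rules side by side**

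- Eligible: breech discovered in labour from 37 weeks, vaginal birth wanted, consent given. Mode of birth plays no part.
- Approached: about 24 hours after birth. The wording covers all labour diagnoses, but the mode of birth is already known.
- Actively searched for: unplanned vaginal breech births.

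If a site follows the named system and does nothing more, every labour-diagnosed woman it finds has delivered vaginally. The stratum's vaginal birth rate is then 100% by construction.

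**2. Illustration for a pooled vaginal birth rate**

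Inputs:

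- s, the share of eligible women diagnosed in labour: 20-30% (section 8). This is a figure for breech presentations at sites without routine third-trimester scans. Using it for the cohort is an assumption.
- a, the vaginal birth rate in women enrolled antenatally: 13/27 = 48.1% (Table 2, OptiBreech 1). Using it here is also an assumption.
- v, the true vaginal birth rate in eligible women diagnosed in labour: not given in the protocol, assumed 30-70%.

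Formulas:

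- All eligible women found: (1 − s)a + sv
- Only labour-diagnosed vaginal births found: [(1 − s)a + sv] / [(1 − s) + sv]

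The second denominator is smaller because the missed caesarean cases drop out of it.

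Middle case, s = 25%, v = 50%:

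- All found: 0.75 × 0.481 + 0.25 × 0.50 = 0.486
- Vaginal births only: 0.486 / (0.75 + 0.125) = 0.556
- In-labour caesarean, using 9/27 from Table 2 for women enrolled antenatally: all found, 0.75 × 0.333 + 0.25 × 0.50 = 0.375; vaginal births only, 0.25 / 0.875 = 0.286

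Vaginal birth rate over the range (differences from unrounded values):

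| s | v | All found | Vaginal births only | Difference (points) |
| --- | --- | --- | --- | --- |
| 20% | 30% | 44.5% | 51.8% | 7.2 |
| 20% | 50% | 48.5% | 53.9% | 5.4 |
| 20% | 70% | 52.5% | 55.9% | 3.4 |
| 25% | 30% | 43.6% | 52.9% | 9.3 |
| 25% | 50% | 48.6% | 55.6% | 6.9 |
| 25% | 70% | 53.6% | 58.0% | 4.3 |
| 30% | 30% | 42.7% | 54.1% | 11.4 |
| 30% | 50% | 48.7% | 57.3% | 8.6 |
| 30% | 70% | 54.7% | 60.1% | 5.4 |

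The overstatement runs from 3.4 to 11.4 points and is upward throughout.

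**3. Direction for safety**

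Take v = 50% within the stratum, with assumed adverse-outcome rates by mode:

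- 4% after vaginal birth and 7% after caesarean: true 0.5 × 4 + 0.5 × 7 = 5.5%, observed 4%.
- 7% after vaginal birth and 4% after caesarean: true 5.5%, observed 7%.
- Equal rates: no difference.

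The net error in a composite can therefore go either way. Harms that occur only at caesarean are under-counted in every case.

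**The case against.** The strongest reply is that the protocol does not restrict identification to vaginal breech births. The approach text covers all labour diagnoses, and the duty on staff to know of the study and refer does not depend on mode of birth. That stands. A reader might infer that caesarean cases are shut out, but the documents show a gap rather than an exclusion. Even so, general awareness is a weaker route than a dedicated search. The staff named as examples in Screening Procedures are those who perform or refer for scans, so caesarean cases would still be found less reliably.

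Eligibility is also narrower than every breech found in labour. The woman must want a vaginal birth, and one who requested a caesarean before recruitment is excluded. Some caesarean cases are rightly absent, so any repair must say otherwise eligible women.

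The reach of the problem is limited too:

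- Women diagnosed in labour cannot be randomised (Trial exclusion criteria), so the randomised comparison is untouched.
- The contrast in Cohort analysis between vaginal breech births with and without OptiBreech care conditions on vaginal breech birth by design. Missing caesarean cases distort neither that contrast nor rates among actual vaginal breech births.
- Section 13 reports mode of birth by care pathway and intended mode. A single pooled vaginal birth rate is not a named output.
- The cohort safety objective in section 5 is worded for women planning a vaginal breech birth with OptiBreech care.
- A reader might infer that the full trial's sample size is contaminated. Secondary Outcomes does say that incidence rates will inform power calculations, but the 2280 in section 13 rests on existing evidence about neonatal admission. No route from this stratum to that figure is stated.

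These points confine the problem to one descriptive, non-randomised stratum and to tables that pool it. They do not remove the mismatch between who is eligible and who is searched for.

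**Conclusion.** The point holds for the labour-diagnosed stratum of the non-randomised cohort. Under the one system named, entry depends on an outcome the study reports. The vaginal birth rate in the stratum tends towards 100%, and caesarean-specific harms in it are under-counted. Any cohort mode-of-birth or intended-mode safety rate that includes it is distorted.

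On the stated assumptions, a pooled vaginal birth rate would be overstated by about 3 to 11 points. This is an illustration at the extreme where no labour-diagnosed caesarean case is found; partial capture through staff referral would reduce it. It also depends on an in-labour vaginal rate the protocol does not supply.

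Two stronger readings are not supported. One is that cohort safety rates are biased in a known direction; part 3 of the working shows that the direction is open. The other is a larger overstatement, obtained by treating 10 to 15 of the 50 estimated cohort women as diagnosed in labour and all delivered vaginally. With 15, for example, that gives (0.48 × 35 + 15)/50 = 63.6%, against (0.48 × 35 + 0.3 × 15)/50 = 42.6% at a true rate of 30%. That sum replaces each missed caesarean with an extra vaginal birth. Missed women simply leave the denominator, and the protocol sets no minimum cohort size that would cause them to be replaced.

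**What to change.** In section 8 (Breech presentation diagnosed in Labour), replace the case-finding sentence with one to this effect: local PIs should establish a system to identify all otherwise eligible women whose breech presentation is first diagnosed in labour from 37 weeks, whatever the mode of birth.

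Add that sites record the numbers identified, approached and consenting by mode of birth, so that any remaining selection can be seen. Report this stratum apart from women enrolled antenatally. The baseline data table in section 12 already captures the point of diagnosis, so separating enrolled women needs no new variable.

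The cost is a wider search of birth records and some extra postnatal consent approaches. Randomisation and the sample size of 104 are not affected.
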